### Data collection and management

2.8

The whole process of data collection and recording will be carried out by 1 or 2 assistants. Personal information about potential participants and registered participants will be collected, shared, and stored in a separate storeroom to protect pre-, during, and post-trial confidentiality. The access to the database will be restricted to the researchers in this study team.

### Statistical analysis

2.9

Data were analyzed using the statistical software package SPSS version 25.0 (Chicago, IL). Continuous variables were described as the mean ± standard deviation, and differences between groups were analyzed using a series of one-way analysis of variance (ANOVA) with Bonferroni's post-hoc test, while differences between groups over time were analyzed using multi-way ANOVA with Bonferroni's post-hoc test. Categorical variables were described as the number (%), and were analyzed by Fisher's exact test. A *P* value of <.05 was considered statistically significant.

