### Interventions

2.6

Before operation, the patients were examined by Doppler ultrasound to determine whether there was venous embolism, and if necessary, additional pulmonary CT was taken to rule out pulmonary embolism. The rivaroxaban group began to take 10 mg, once a day, 6 to 8 hours after operation, while the dabigatran etexilate group began to take 1 to 4 hours after operation, which was halved at the first time, and recovered to 220 mg once a day the next day. Both course of treatments lasted for 2 weeks.

Ultrasonic Doppler examination of limbs was performed by ultrasound doctors at 1 or 2 weeks after operation. If the formation of DVT is suspected, ultrasonic Doppler examination should be performed immediately; if pulmonary embolism is suspected, pulmonary CT or angiography should be performed in addition to ultrasonic Doppler examination, and the results should be recorded. The patients were followed up for 30 to 35 days after the last administration. Hematological examination was performed before operation, on the same day after operation and before discharge, and abnormal laboratory indexes were monitored. Hematological and imaging tests could also be performed during follow-up if necessary.

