### Outcome measures

2.7

(1)Validity index: The primary outcome is a combination of total VTE (venography or symptomatic DVT and/or PE) and all-cause mortality during treatment, which is defined as the time from the date of the first study to 3 days after the last administration, and the secondary outcome is a combination of major VTE (venography or symptomatic proximal DVT and/or PE) and VTE-related mortality during treatment.(2)Security index: The main safety outcome is the incidence of massive hemorrhage from the first medication in the study to 2 days after the last use (continued treatment). Massive hemorrhage is defined as clinically fatal bleeding that occurs in critical organs (such as retroperitoneal, intracranial, intraocular, or intraspinal), requiring surgery, outside the surgical site, and associated with it. The secondary safety outcome was the incidence of clinically related non-major bleeding events, defined as polyphyly hemorrhage, accidental hematoma (>25 cm^2^), excessive wound hematoma, epistaxis (>5 min), gingival bleeding (>5 min), gross hematuria, rectal bleeding, cough or hematemesis, vaginal bleeding, semen bleeding, traumatic intra-articular bleeding, or surgical site bleeding, etc. Secondary safety outcomes also include the incidence of adverse reactions, such as abnormal laboratory indicators (with special emphasis on liver and kidney function indicators), allergic reactions, and other adverse events.

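### The over-time comparison of continuous data is planned as a multi-way ANOVA with no within-patient term; run as written on the three blood samples per patient, it would under-detect differential change between the drugs

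*Protocol article*

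**What the plan says.** Section 2.9 (Statistical analysis) of the protocol article summarises continuous data by mean and standard deviation. It compares groups by one-way ANOVAs with a Bonferroni post-hoc test, and continues: "while differences between groups over time were analyzed using multi-way ANOVA", again with a Bonferroni post-hoc test. No variable is named for this analysis. Neither a repeated-measures design nor a patient factor, random effect or correlation structure is mentioned. Categorical variables go to Fisher's exact test, and the significance threshold is P < .05.

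Section 2.6 (Interventions) gives the sampling schedule: "Hematological examination was performed before operation, on the same day after operation and before discharge". Further samples are optional: "Hematological and imaging tests could also be performed during follow-up if necessary". No other continuous measurement repeated over time is described.

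Section 2.7 (Outcome measures) lists the laboratory data as a rate, not a mean: "Secondary safety outcomes also include the incidence of adverse reactions, such as abnormal laboratory indicators", with liver and kidney function singled out.

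Sections 2.3 and 2.5 give 600 participants, 300 per arm, allocated 1:1.

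**The concern.** An ordinary multi-way ANOVA with factors group and time assumes that all values are independent. Three values from one patient are not: a patient with a high preoperative creatinine will tend to have a high one at discharge. Ignoring this puts the wrong error term under both tests of interest, and the two errors run in opposite directions.

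- The group main effect is a between-patient comparison, so its P values come out too small.
- The group × time effect is a within-patient comparison, so its P values come out too large.

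For laboratory safety the second matters more, because it asks whether values change differently under the two drugs. The group main effect is also a poor target here, since it averages in a preoperative value that treatment cannot have influenced.

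**Working it through.** **Inputs.** From the article: 300 patients per arm, three scheduled samples per patient, nominal α = 0.05. The article gives no within-patient correlation ρ, so ρ is assumed, equal between all pairs of times, and shown over a range. Equal variance at the three times is also assumed.

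**The plan's own figure.** The only stated figure that bears on this point is the 5% threshold. At ρ = 0 the calculation returns it: about 5.0% for both tests. The sample size has no stated inputs and cannot be reproduced.

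**Formulas.** Let σ² be the variance of one value. The pooled error mean square of the independent-values ANOVA estimates σ². Under the null hypothesis:

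- the group mean square has expectation σ²(1 + 2ρ), so true type I error ≈ 2 × [1 − Φ(1.96 / √(1 + 2ρ))];
- the group × time mean square (2 df) has expectation σ²(1 − ρ), so true type I error ≈ P(χ²₂ > 5.991 / (1 − ρ)).

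At ρ = 0.5, the group test gives 1.96 / √2 = 1.386, hence 0.166. The group × time test gives 5.991 / 0.5 = 11.98, hence 0.0025.

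| ρ (assumed) | Group effect, formula | simulated | Group × time, formula | simulated | Group × time with within-patient error term, simulated |
|---|---|---|---|---|---|
| 0 | 0.050 | 0.050 | 0.050 | 0.048 | 0.048 |
| 0.3 | 0.121 | 0.120 | 0.0139 | 0.0138 | 0.051 |
| 0.5 | 0.166 | 0.173 | 0.0025 | 0.0028 | 0.054 |
| 0.7 | 0.206 | 0.203 | 0.00005 | 0.0003 | 0.048 |

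The simulations used 300 per arm and 4,000 trials per ρ. The last column is a repeated-measures ANOVA on the same data and stays close to 5%.

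**Power.** For an assumed true difference of 0.2 SD at the last sample only (2,000 simulated trials), power of the group × time test is:

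| ρ | Independent-values ANOVA | Within-patient error term |
|---|---|---|
| 0.5 | 32% | 72% |
| 0.7 | 24% | 91% |

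**What is not distorted.** The difference between arm means at one visit has variance 2σ²/300, and the pooled error term estimates σ² correctly. Its simulated type I error was 0.047 to 0.054 for ρ from 0 to 0.7. Testing all three visits without correction gave a family-wise error of 0.11 to 0.14; Bonferroni over the three visits gave 0.038 to 0.049.

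**Preoperative adjustment.** With correlation ρ to the preoperative value, covariate adjustment lowers residual variance by ρ²: 25% at 0.5 and 49% at 0.7.

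**The case against.** **The defined laboratory outcome is not a mean.** Section 2.7 counts abnormal results, which section 2.9 sends to Fisher's exact test. A reader might infer that the trial's laboratory-safety conclusion would be wrong in both directions. The article does not support that: no mean laboratory value, or change in one, is named as an outcome. This stands and limits the reach of the point. The over-time test is still prescribed, however, and the Discussion says the study will supply data on changes in measurements.

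**The link to blood tests is inferred.** Section 2.9 names no variable. This also stands, although the article describes no other repeated continuous measurement to which the sentence could apply.

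**Multi-way ANOVA may be loose wording.** A repeated-measures ANOVA may have been meant, with its error term left to a plan that is not shown. That is possible, and the finding is therefore conditional on the method being run as written. But the article names a method, and nothing in it points to a within-patient term. If one was intended, a short phrase resolves the matter.

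**Not every P value is wrong, and Bonferroni is not idle throughout.** Both parts are correct. Single-visit contrasts keep about the right error rate. A reader might conclude from the two-arm design that the Bonferroni step has nothing to do anywhere. It is empty only for the two-level group factor; across three times it can provide real multiplicity control.

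**Baseline adjustment corrects no error.** Unadjusted comparison is valid in a randomised trial, so the preoperative covariate is a gain in precision only. Log-transforming skewed enzymes is likewise optional.

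**Conclusion.** The point holds in a limited form. Run as written on three samples per patient, the multi-way ANOVA gives a group main effect that is significant too often (about 12% to 21% instead of 5%). Its group × time test is almost never significant under the null (about 1.4% to below 0.1%), with a corresponding loss of power to detect differential change.

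These sizes rest on an assumed, equal within-patient correlation of 0.3 to 0.7 and on equal variances over time. At zero correlation there is no error, and at every positive value tried both errors appear. That the method applies to laboratory values is inferred.

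The damage is confined to supportive continuous laboratory analyses. The primary composite of venous thromboembolism and death, the bleeding outcomes and the incidence of abnormal laboratory values are all categorical and unaffected.

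**What to change.** In section 2.9, name the laboratory variables concerned and replace the multi-way ANOVA by one of the following, for each variable:

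- a linear mixed model for repeated measures with the postoperative values as outcome; arm, time, arm × time and the preoperative value as fixed effects; and correlation within patient; or
- ANCOVA of the pre-discharge value on arm and the preoperative value.

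Make the pre-discharge contrast between arms the main one. Section 2.6 starts rivaroxaban 6 to 8 hours and dabigatran 1 to 4 hours after operation and gives no hour for the same-day sample. That sample may therefore precede the first dose, possibly in one arm only.

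Drop the Bonferroni post-hoc test for the two-group comparison, where there is nothing to correct, and keep a multiplicity correction wherever several times are compared.

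If a repeated-measures analysis was meant all along, say so and state the error term. The cost is about two sentences. Both models are available in SPSS 25, the software already named, and no new data or patients are needed.

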## Discussion

3

Although current preventive measures can play a good role in treatment, there is still a high incidence of VTE after hip replacement and knee replacement.^[10]^ Low molecular weight heparin is mostly used in the prevention of venous thrombosis, but daily subcutaneous injection brings inconvenience to patients. Therefore, in recent years, new anticoagulants have attracted much attention of clinicians because of their high specificity and oral characteristics.

National Institute for Health and Care Excellence (NICE) guidelines recommend rivaroxaban should start preventing at 6 to 12 hours postoperatively, total hip arthroplasty (THA) should prevent for 28 to 35 days, total knee arthroplasty (TKA) should prevent for 10 to 14 days.^[11]^ American College of Chest Physicians (ACCP) recommends rivaroxaban prophylaxis at 6 to 8 hours postoperatively in 2012, and the prophylaxis time for hip or knee arthroplasty should be no less than 10 to 14 days, which can be extended to 35 days.^[5]^ Rivaroxaban is a highly selective, oral direct factor Xa inhibitor. Inhibitor Xa can inhibit the endogenous and exogenous pathways of blood clotting waterfall, thus reduce the production of thrombin and inhibit thrombosis.^[12]^ Dabigatran etexilate belongs to β-alanine thrombin inhibitor, which is a new and synthetic direct thrombin inhibitor and the prodrug of dabigatran.^[13]^ The basic principle is that direct thrombin inhibitors bind to the activation sites of thrombin to inhibit thrombin and inhibit the conversion of fibrinogen to fibrin, as well as activating factor 5 (FVa), activating factor 8 (FVIIIa), activating factor 9 (FIXa), activating factor 13 (FXIIIa), and platelet kinase activating receptor, which then blocks the final steps of the clotting cascade mesh and thrombosis.^[14]^ In 2013, the European Medicines Agency have approved the phase III clinical trial of dabigatran etexilate for the prevention of venous thrombosis after hip or knee arthroplasty.

At present, as a new type of oral anticoagulant, rivaroxaban and dabigatran etexilate have been used in the prevention and treatment of postoperative venous thrombosis. Many countries have carried out randomized controlled trials compared with conventional anticoagulants injected with low molecular weight heparin,^[15–17]^ but there is no comparative study on the efficacy and safety of the 2. The results of this study will suggest clinical evidence comparing taking rivaroxaban with taking dabigatran etexilate orally by providing data about the changes in various measurements from the rigorously conducted. This study will provide a basis for clinicians to choose acupoint injection or sacral canal injection to treat LDH.

This study also has the following limitations: because this is a single-center randomized controlled study, there may be regionalization in the included population, and there may be a certain bias in the results; factors such as the age and cause of disease of the patients included in the study may affect the results to a certain extent.
